### Study design

The study is a parallel-group, prospective, randomized clinical trial with an adaptive two-stage phase II trial design (including a sample size recalculation at the interim analysis) for patients with extremity soft tissue sarcoma, randomized to one of the two treatment arms (arm A: proton therapy, arm B: carbon ion therapy). The total dose of 39 Gy (RBE) in 13 fractions will be prescribed in both arms. The accrual period of this trial will take approximately 2 years with a follow-up time of 12 months for each patient. Patients meeting the eligibility criteria and willing to participate will give written informed consent and will be enrolled at Heidelberg University Hospital.

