### Secondary endpoints

The effectiveness of treatment is examined by regular MRI of the according extremity and thoracic CT follow-ups. Local control rate depicts the freedom from local progression. Local progression-free survival is defined as the survival probability from the beginning of radiotherapy until local progression. Disease-free survival is defined as the time from the beginning of radiotherapy until local or distant progression. The overall survival is defined as the time from the beginning of radiotherapy until the date of death due to any reason, until the end of the observation period or until the date of the last presentation in case the patient is lost to follow-up (censoring).

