Given these probabilities of success for the alternative and null hypothesis for the protons and carbon ion group, a statistical power of 1-β = 0.80 and a one-sided Type I error rate α = 0.05 for each of the two comparisons, the expected sample size under the null hypothesis is 25.59 and under the alternative hypothesis it amounts to 29.97; the maximum sample size in this design is 52. The interim analysis is performed when the data of 21 patients are available and therefore this is the minimum sample size. The recalculated sample sizes for stage 2 in both treatment arms depend on the patient number with a treatment success (no wound complications and no discontinuation). These values as well as the boundaries for early stopping and the decision boundaries after stage two are calculated according to Kunzmann and Kieser [19] with program code supplied by the authors. The estimation of success rates in both study arms is performed by calculation of point estimators [21] and calculation of two-sided 95%-Clopper-Pearson-type confidence intervals that take the adaptive two-stage design into account [22].

Analysis of the secondary time-to-event endpoints LPFS, DFS, and OS will be performed by the Kaplan–Meier method, patients without event will be censored. The treatment groups are compared using the logrank test. Quality of life will be measured by the EORTC-QLQ30 questionnaire and assessed by presentation of mean, standard deviation, median, minimum, and maximum as well as application of a two-sample t test. For the secondary endpoint local control, absolute and relative frequencies are calculated for each treatment group together with two-sided 95% Agresti–Coull confidence intervals, and an unconditional fourfold table test will be applied for treatment group comparison. Adverse and serious adverse events will be listed, and absolute and relative frequencies will be calculated.

The primary analysis for the primary and secondary endpoints is based on the intention-to-treat set including all study patients fulfilling the inclusion/exclusion criteria and having been treated for at least 1 week. Additionally, a per-protocol analysis is performed as sensitivity analysis which is based on all patients who have received the treatment as planned and for whom the relevant data is available. Safety endpoints are evaluated for all study patients for which the treatment has started.

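### As defined, disease-free survival (and, on its plainest reading, local progression-free survival) censors deaths without progression, so the curves overstate the proportion alive and disease-free

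*Protocol article*

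**What the plan says.** The definitions stand together in the protocol article under Secondary endpoints:

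- DFS: "Disease-free survival is defined as the time from the beginning of radiotherapy until local or distant progression".
- LPFS: "Local progression-free survival is defined as the survival probability from the beginning of radiotherapy until local progression".
- Local control: "Local control rate depicts the freedom from local progression".
- OS: "The overall survival is defined as the time from the beginning of radiotherapy until the date of death due to any reason", with censoring at the end of observation or at the last visit.

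The analysis is under Statistical methods: "Analysis of the secondary time-to-event endpoints LPFS, DFS, and OS will be performed by the Kaplan–Meier method, patients without event will be censored". For the comparison of arms: "The treatment groups are compared using the logrank test". Study design gives a "follow-up time of 12 months for each patient".

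The article gives no competing-risk method. It gives no expected rate, event count or power for LPFS or DFS. The stated error rates and sample sizes belong to the binary primary endpoint.

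**The concern.** Death is named as an event in one definition and not in the other two. With a rule that censors everyone who lacks the event, a patient who dies without recorded progression leaves the DFS analysis as a censored case. Kaplan–Meier then treats that patient as someone who could still progress later, like a patient who is alive and has merely reached the end of follow-up.

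Readers take DFS and LPFS as the proportion alive without disease or without local disease. A curve that ignores deaths answers a different question and is more favourable. LPFS is the more exposed of the two if its sentence is read in the same way, because a death after distant spread but without local failure is then not an event either.

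The log-rank tests on these endpoints compare only the rate of progression between protons and carbon ions. Deaths enter those tests only by leaving the risk set.

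**Working it through.** The plan has no figure of its own to reproduce here. The check is a reading of the definitions, then arithmetic on assumed event rates.

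**1. Reading.** The DFS event is local or distant progression. The LPFS event, on the plainest reading, is local progression. The OS event is death from any cause. A patient who dies with no recorded progression therefore has an OS event and no DFS event, and the censoring rule applies.

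**2. General size.** Let p be the 12-month progression risk and d the 12-month risk of death without progression, each under a constant hazard (assumptions).

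- As written: DFS = 1 − p.
- With death as an event: DFS = (1 − p)(1 − d).
- Overstatement = (1 − p) × d.

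Overstatement in percentage points:

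| p | d = 2% | d = 5% | d = 10% |
|---|---|---|---|
| 5% | 1.9 | 4.8 | 9.5 |
| 10% | 1.8 | 4.5 | 9.0 |
| 20% | 1.6 | 4.0 | 8.0 |
| 30% | 1.4 | 3.5 | 7.0 |

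For p = 10%, DFS as written is 90.0%, against 88.2%, 85.5% and 81.0% with death counted.

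**3. One arm by hand.** Assume 30 patients, close to the expected sample size of 29.97 under the alternative hypothesis. Three die without progression, at months 4, 7 and 9. The rest are followed to month 14 from the start of radiotherapy. That horizon fits the schedule: 2 to 3 weeks of radiotherapy, 4 to 6 weeks to resection, then 12 months.

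- LPFS with one local progression at month 10: as written, 27 are at risk, so 26/27 = 96.3%. With death counted, 26/30 = 86.7%. OS = 27/30 = 90.0%, so LPFS as written lies above OS.
- DFS with five progressions at months 5, 6, 8, 10 and 11: as written, 27/29 × 25/26 × 22/24 = 82.1%. With death counted, 22/30 = 73.3%. Here DFS as written lies below OS (90.0%).

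**4. When the curve passes OS.** It happens roughly when deaths without progression are as frequent as progressions or more so. In the constant-hazard model with no deaths after progression, p = 5% and d = 10% give DFS as written 95.0% and OS 90.2%. With p = 20% and d = 2% they are 80.0% and 98.2%.

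**5. Two arms.** Assume 30 per arm, three progressions per arm at month 9 (all alive at month 12), and 0 versus 4 deaths without progression at month 3.

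| Endpoint at 12 months | No deaths | Four deaths | Log-rank χ² (1 df) | p |
|---|---|---|---|---|
| DFS as written | 27/30 = 90.0% | 23/26 = 88.5% | 0.034 | 0.85 |
| DFS with death counted | 27/30 = 90.0% | 23/30 = 76.7% | 2.13 | 0.14 |
| OS | 30/30 = 100% | 26/30 = 86.7% | 4.21 | 0.04 |

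As written, the DFS test uses only the six events at month 9, with 30 and 26 at risk. The expected count in the first arm is 6 × 30/56 = 3.21 against 3 observed. The variance is 6 × (30/56) × (26/56) × (50/55) = 1.357, so χ² = 0.214²/1.357 = 0.034. Counting the deaths adds a difference of 0 − 2 = −2 at month 3, with variance 4 × ¼ × 56/59 = 0.949. That gives χ² = 2.214²/2.306 = 2.13.

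**The case against.** Several points can be made for the plan, and some of them stand.

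- **The LPFS sentence is ambiguous.** It describes a survival probability rather than a time, and it can be read as surviving without local progression. This stands: for LPFS, the censoring of deaths is the plainest reading and not a certainty. It does not help DFS, which is a time to progression only, and the LPFS sentence would need the same repair.
- **The article is a condensation, and the full protocol may say more.** That would excuse an omission. Here the definitions are stated, and death is named under OS in the same paragraph.
- **Time to progression with deaths censored is a legitimate analysis.** It is, as a comparison of progression hazards and under that name. It is not DFS, and its Kaplan–Meier curve does not give the proportion alive and disease-free.
- **The effect may be small.** This stands. Stage IV and nodal disease are excluded, the Karnofsky index must be at least 70%, and follow-up is 12 months. At 2% death and 10% progression the overstatement is 1.8 points.

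A reader might also infer more than the article supports:

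- That a death imbalance between the arms is hidden. It is not. OS counts every death and has its own log-rank test; in the two-arm example OS shows the imbalance (p = 0.04).
- That flawed LPFS or DFS estimates will feed the planned phase III. The article says only that the later trial will compare the arms on local control, which is analysed here separately as a proportion.
- That LPFS merely repeats local control. On the plainest reading the event is the same, but local control is analysed as frequencies with Agresti–Coull intervals and a fourfold table test. LPFS adds time and censoring.

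**Conclusion.** The point holds. As written, a death without recorded progression is censored for DFS and, on the plainest reading, for LPFS. Neither curve then shows the proportion alive and free of (local) disease.

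The overstatement is about 1.4 to 9.5 percentage points for an assumed 12-month risk of 2 to 10% for death without progression and 5 to 30% for progression. The range rests wholly on those assumed rates and on constant hazards. A curve above OS is possible but not inevitable, and the LPFS example that shows it assumes three deaths against one local progression.

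The loss of sensitivity to deaths is confined to the DFS and LPFS tests. All analyses are declared descriptive and both endpoints are secondary, so the primary endpoint, the sample size and the interim decisions are untouched. It is a definition to correct before these endpoints are analysed, not a threat to the trial's main conclusion.

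**What to change.** In Secondary endpoints, define LPFS as the time from the start of radiotherapy to local progression or death from any cause, whichever comes first. Define DFS as the time from the start of radiotherapy to local or distant progression or death from any cause. In Statistical methods, limit censoring for both to patients who are alive and event-free. The Kaplan–Meier and log-rank methods can stay as they are.

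If a disease-only quantity is wanted, rename the endpoints time to local progression and time to progression, and report the cumulative incidence of each with death as a competing event.

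The cost of the first option is wording: two definitions and one censoring rule, with no extra data, because deaths are already collected for OS. The downside is that the reported rates become somewhat less favourable, by the amounts in the table if the assumed rates apply. The alternative also needs a cumulative-incidence estimator in place of Kaplan–Meier. Either change should be made before the secondary analyses are run, so that it is not a redefinition after the data are seen.

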### Statistical methods

This study is performed to deliver basic data for the neoadjuvant hypofractionated carbon ion or proton radiation treatment of patients with extremity soft tissue sarcoma by providing safety and toxicity data for the here presented treatment regimen. The framework of the safety and feasibility considerations is the current standard neoadjuvant normofractionated photon radiotherapy; it is considered as the historical cohort which served for the planning of this pilot study. The randomization will be performed as block randomization at a ratio of 1:1 aiming at equal group sizes by using a web-based randomization tool (randomizer.at).

Due to the pilot character of the trial, all analyses are performed descriptively and the results are to be interpreted accordingly. The primary endpoint is assessed separately in each of the two treatment groups by applying an optimal adaptive two-stage phase II-design with one interim analysis according to Kunzmann and Kieser [19]. This design is an adaptive variant of Simon’s design [20], where the sample size of stage two is chosen optimally based on the results of the interim analysis. It offers the possibility to prematurely terminate the study due to futility or early success at the timepoint of the interim analysis or allows data-driven recalculation of sample size for the second part of the study while adhering to the specified Type I and Type II error rates. The randomization will be performed as block randomization at a ratio of 1:1. After the interim analysis, dependent on the results, different sample sizes in both treatment arms may be required and the randomization ratio would then be adjusted accordingly. Under the null hypothesis, we would expect in both groups wound complications or dicontinuations to occur in ≥35% of the treated patients within 120 days after surgery, so the expected probability of patients with no wound complications and no discontinuation would be π ≤ 65% for both protons as well as carbon ions. Under the alternative hypothesis, we would expect less than 15% of the patients to have wound complications or discontinue therapy within 120 days after surgery with π ≥ 85% being the rate of patients without wound complications or discontinuation within 120 days after surgery.

Given these probabilities of success for the alternative and null hypothesis for the protons and carbon ion group, a statistical power of 1-β = 0.80 and a one-sided Type I error rate α = 0.05 for each of the two comparisons, the expected sample size under the null hypothesis is 25.59 and under the alternative hypothesis it amounts to 29.97; the maximum sample size in this design is 52. The interim analysis is performed when the data of 21 patients are available and therefore this is the minimum sample size. The recalculated sample sizes for stage 2 in both treatment arms depend on the patient number with a treatment success (no wound complications and no discontinuation). These values as well as the boundaries for early stopping and the decision boundaries after stage two are calculated according to Kunzmann and Kieser [19] with program code supplied by the authors. The estimation of success rates in both study arms is performed by calculation of point estimators [21] and calculation of two-sided 95%-Clopper-Pearson-type confidence intervals that take the adaptive two-stage design into account [22].

Analysis of the secondary time-to-event endpoints LPFS, DFS, and OS will be performed by the Kaplan–Meier method, patients without event will be censored. The treatment groups are compared using the logrank test. Quality of life will be measured by the EORTC-QLQ30 questionnaire and assessed by presentation of mean, standard deviation, median, minimum, and maximum as well as application of a two-sample t test. For the secondary endpoint local control, absolute and relative frequencies are calculated for each treatment group together with two-sided 95% Agresti–Coull confidence intervals, and an unconditional fourfold table test will be applied for treatment group comparison. Adverse and serious adverse events will be listed, and absolute and relative frequencies will be calculated.

The primary analysis for the primary and secondary endpoints is based on the intention-to-treat set including all study patients fulfilling the inclusion/exclusion criteria and having been treated for at least 1 week. Additionally, a per-protocol analysis is performed as sensitivity analysis which is based on all patients who have received the treatment as planned and for whom the relevant data is available. Safety endpoints are evaluated for all study patients for which the treatment has started.

Statistical analysis will be performed by the statistical software SAS v9.4 (SAS Institute, Cary, NC).

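### The printed sample sizes are not those of the optimal design at the stated one-sided α of 0.05 per arm; they match the design for α = 0.025

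*Protocol article*

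**What the plan says.** In Statistical methods, the protocol article assesses the primary endpoint separately in each arm with an optimal adaptive two-stage design that allows early stopping for futility or success. The null is "the expected probability of patients with no wound complications and no discontinuation would be π ≤ 65" per cent and the alternative is given "with π ≥ 85% being the rate of patients without wound complications or discontinuation". The error rates are "a statistical power of 1-β = 0.80" and a "one-sided Type I error rate α = 0.05 for each of the two comparisons".

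From these inputs the article derives the expected sample size, which "under the null hypothesis is 25.59 and under the alternative hypothesis it amounts to 29.97; the maximum sample size in this design is 52". It adds: "The interim analysis is performed when the data of 21 patients are available and therefore this is the minimum sample size".

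Stage-two sizes, stopping boundaries and final decision boundaries are not printed; they are said to come from the program code of the cited method. Success rates are to be reported with "two-sided 95%-Clopper-Pearson-type confidence intervals" adapted to the design. The section gives no α of 0.025, no two-sided test of the primary endpoint and no split of α between the arms.

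**The concern.** The sizes are presented as the result of α = 0.05 and power 0.80, so a reader should be able to recover them from those inputs. A quick check suggests otherwise. At α = 0.05 a fixed single-stage exact test needs only 31 patients per arm, so an optimised adaptive design that expects about 30 under the alternative and may run to 52 would save almost nothing.

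Because the boundaries are not printed, the stated α is the reader's only guide to the decision rule. Anyone who reruns the calculation with that α obtains different stopping rules and stage-two sizes from those of the design behind the printed numbers. The stage-two sizes also matter for the randomisation ratio, which the article says may be adjusted after the interim.

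**Working it through.** **Inputs** (Statistical methods): π0 = 0.65, π1 = 0.85, stated one-sided α = 0.05, power 0.80, interim at n1 = 21. The sizes are read as per arm, since each arm is assessed separately.

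**Formulas.** Let b(x) be the binomial probability of x successes in 21, n(x) the total size after x, and c(x) the total number of successes needed.

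- E[N] = 21 + Σ b(x)·(n(x) − 21)
- P(declare success) = P(X ≥ early-success limit) + Σ b(x)·P(Bin(n(x) − 21, π) ≥ c(x) − x), summed over the counts that continue

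**Step 1: reproduce the printed figures.** An exact integer programme at α = 0.025 and power 0.80, minimising E[N] under the alternative, gives n1 = 21, futility at ≤15 and success at ≥19. The other counts continue as follows:

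| x | n(x) | c(x) | b(x) at 0.65 | success in stage 2 at 0.65 | b(x) at 0.85 | success in stage 2 at 0.85 |
|---|---|---|---|---|---|---|
| 16 | 52 | 42 | 0.10852 | 0.01775 | 0.11474 | 0.68266 |
| 17 | 38 | 31 | 0.05927 | 0.10279 | 0.19123 | 0.75561 |
| 18 | 30 | 25 | 0.02446 | 0.33727 | 0.24081 | 0.85915 |

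P(X ≥ 19) is 0.00862 at 0.65 and 0.37050 at 0.85. The stage-two additions are 31, 17 and 9 patients. Products below use unrounded probabilities.

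- E[N] at 0.65 = 21 + 3.3640 + 1.0077 + 0.2202 = 25.592 (printed 25.59)
- E[N] at 0.85 = 21 + 3.5568 + 3.2509 + 2.1672 = 29.975, unrounded 29.97496 (printed 29.97)
- Maximum 52 and n1 = 21 (both as printed)
- Type I error = 0.00193 + 0.00609 + 0.00825 + 0.00862 = 0.0249
- Power = 0.07833 + 0.14449 + 0.20689 + 0.37050 = 0.8002

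Neighbouring interim sizes are worse under the same objective: E[N] at 0.85 is 30.23 for n1 = 20 and 30.08 for n1 = 22.

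**Step 2: the stated α and other settings.**

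| α | power | minimised under | n1 | E[N] null | E[N] alternative | maximum |
|---|---|---|---|---|---|---|
| 0.05 | 0.80 | alternative | 18 | 25.44 | 23.37 | 46 |
| 0.05 | 0.80 | alternative, consecutive continuation counts only | 17 | 20.63 | 23.54 | 36 |
| 0.05 | 0.80 | alternative, n1 fixed | 21 | 23.10 | 24.25 | 36 |
| 0.05 | 0.80 | null | 9 | 17.24 | 34.63 | 48 |
| 0.05 | 0.80 | null, n1 fixed | 21 | 22.31 | 25.17 | 31 |
| 0.05 | 0.90 | alternative, n1 fixed | 21 | 31.63 | 29.40 | 64 |
| 0.03 | 0.80 | alternative, n1 fixed | 21 | 24.59 | 28.44 | 42 |

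None of these gives 21 / 25.59 / 29.97 / 52.

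**Step 3: check without an optimiser.** The smallest single-stage exact test at α = 0.05 has n = 31 with at least 25 successes (type I error 0.046, power 0.827). At α = 0.025 it needs 41. An expected size of 29.97 is a real saving only against 41.

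**Step 4: consequence for the rule.** At α = 0.05 with n1 = 21 the optimum is: 16 → 36 (need 29), 17 → 29 (need 24), ≥18 immediate success.

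- Type I error = 0.00670 + 0.01002 + 0.03309 = 0.0498
- Power = 0.06933 + 0.12567 + 0.61130 = 0.806

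The two rules therefore differ at 18/21, which has probability 0.241 at π = 0.85.

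**Step 5: error across two independent arms.** 1 − (1 − 0.02489)² = 0.049 for the matching design, against 1 − 0.95² = 0.0975 if each arm is tested at 0.05.

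**The case against.** The strongest reply is that a design with type I error 0.0249 also satisfies a limit of 0.05, and its power is 0.80, so the article's claim to keep the specified error rates holds as a bound. That stands: the mismatch is conservative, and a reader who inferred an inflated type I error would be wrong. Re-solving at 0.05 would raise the per-arm error from about 2.5% to about 5%, which is the rate the article already declares.

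A reader might also infer that the trial's boundaries are wrong. The documents do not support this. No boundary is printed, and if the program output is the source of the printed sizes, the boundaries in it belong to the same design. The harm arises only if someone recalculates with the stated α.

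Nor is the two-sided 95% interval a separate error. Using it for estimation beside a one-sided 5% test is a choice, and it agrees with a one-sided 0.025 in any case.

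It would be too strong to say that only 0.025 can produce the figures. The match rests on the settings tried and on an objective (expected size under the alternative) that the article does not name. The reason for 0.025 is also open: a split of 0.05 across two arms and a two-sided 5% convention explain it equally well.

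Finally, the article calls all analyses descriptive because the trial is a pilot. That lowers the stakes, but the same section still builds formal stopping and decision rules on this α.

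None of this removes the mismatch. The article prints an input and results said to follow from it, and they do not.

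**Conclusion.** The point holds: the stated one-sided α of 0.05 per arm and the printed sizes do not describe the same optimal design. The sizes agree in all four numbers with α = 0.025, power 0.80 and minimisation under the alternative. At the stated α the expected size under the alternative would be about 6.5 patients per arm lower (29.97 − 23.5 ≈ 6.5).

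This assumes exact binomial calculation, sizes per arm and the article's 65% and 85%. A chance match of four numbers at a conventional α is unlikely, but only the sponsor's program output can confirm the α used.

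The point should be fixed, but it does not show inflated error or a wrong boundary. The risk is a later recalculation at 0.05 that departs from the design the trial was sized for.

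**What to change.** 1. Check the program output for the α and the objective that produced the printed sizes.
2. If those sizes are kept, restate the per-arm one-sided α as the value used (0.025 on this evidence), with the sponsor's own reason for it. This changes wording only; no patient numbers change.
3. If 0.05 per arm was intended, recompute and restate the interim size, both expected sizes and the maximum. This costs a rerun of the program and changes the planned numbers.
4. In either case, use the boundary table belonging to that same α at both the interim and the final analysis.

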## Methods

### Primary objective

The primary objective of this trial is the evaluation of safety and feasibility of neoadjuvant hypofractionated irradiation in patients with extremity sarcoma using ions (protons or carbon ions) in raster scan technique. The primary endpoint is defined as the rate of wound healing disorders from beginning of radiotherapy to maximum 120 days after the planned tumor resection or discontinuation for any reason related to the treatment.

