### Toxicity, safety, and quality of life

Adverse events and toxicity will be reported according to International Common Terminology Criteria for Adverse Events (CTCAE) version 5.0 system. The results of clinical examinations as well as imaging studies (MRI or CT) will be included. Each patient will pass a baseline clinical examination after enrollment. Patients are monitored continuously during treatment, acute adverse events will be documented weekly as well as at the end of treatment. MRI of the according extremity will be planned 3 weeks and the resection 4–6 weeks after the end of radiotherapy. The first clinical follow-up presentation is 6 weeks after resection. Hereinafter all follow-ups include imaging studies and are performed 3, 6, 9, and 12 months after the tumor resection (Table 1). The criteria for feasibility and safety are fulfilled, if the rate of wound healing complications within 120 days after surgery is below 15% and if the therapy was not canceled, unless the reason for canceling is clearly not treatment related.

**Table 1 Tab1:** Time flow of procedures and examinations

	Study inclusion	Prior to RT	During RT	At the end of RT	3 wk. after RT	OP: 4-6 wk. after RT	6 wk. after RT	3 mo. after OP	6 mo. after OP	9 mo. after OP	12 mo. after OP
Inclusion and exclusion criteria	x										
Informed consent	x										
Medical history	x		x	x	x		x	x	x	x	x
Evaluation of symptoms and toxicity	x		x	x	x		x	x	x	x	x
Radiotherapy			x								
Resection						x					
MRI extremities		x			x			x	x	x	x
CT Thorax		x						x	x	x	x
Quality of life (QLQ-C30)		x			x			x			x

Quality of life (QoL) will be assessed by EORTC QLQ-C30 questionnaires. Repetitive completion of the forms is scheduled before treatment, 3 weeks after the end of radiotherapy, 6 months after surgery, and at the end of the study 12 months after surgery. Statistical analysis will be performed after complete acquisition of data. Changes in QoL before and after radiotherapy and before and after surgery will be determined. The two arms of the study will be compared after the end of radiation and at the end of the whole study.

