### Regular study end

The estimated period of patient accrual is 2 years. The regular end of treatment for the individual patient is 2 to 3 weeks after beginning of radiation therapy (13 fractions, 5–6 fractions per week). The regular study end for each patient is after 12 months after surgery. Patients will be then monitored by regular follow-ups according the current guidelines.

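### The one-week minimum in the primary analysis set leaves out early treatment-related stops that the primary endpoint counts as failures

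*Protocol article*

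**What the plan says.** All places are in the protocol article.

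- **Analysis set (Statistical methods).** The primary and secondary endpoints are analysed in the "intention-to-treat set including all study patients fulfilling the inclusion/exclusion criteria and having been treated for at least 1 week". The only sensitivity analysis is per protocol, limited to patients treated according to plan and with the relevant data. A third set is reserved for safety: "Safety endpoints are evaluated for all study patients for which the treatment has started".
- **Endpoint (Primary objective).** The endpoint has two components. One is wound healing disorders, counted from the start of irradiation until at most 120 days after the planned operation. The other is "discontinuation for any reason related to the treatment".
- **Feasibility criterion (Toxicity, safety, and quality of life).** Besides a wound complication rate below 15%, feasibility is met only "if the therapy was not canceled, unless the reason for canceling is clearly not treatment related".
- **Design (Statistical methods).** The stage 2 sample sizes "depend on the patient number with a treatment success (no wound complications and no discontinuation"). The null hypothesis expects wound complications or "dicontinuations to occur in ≥35% of the treated patients within 120 days after surgery".
- **Length of treatment (Regular study end).** Treatment ends "2 to 3 weeks after beginning of radiation therapy (13 fractions, 5–6 fractions per week").

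**The concern.** The endpoint and the analysis set do not fit together. The endpoint clock starts with radiotherapy, so week 1 is inside the window. The null failure rate of 35% is set for treated patients, with no minimum duration. A treatment-related stop in week 1 thus counts against the regimen under the endpoint definition, but the patient is removed under the definition of the set.

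Week 1 is a sizeable part of a short course: 5/13 = 38% to 6/13 = 46% of the fractions. Early intolerance is also something the discontinuation component is there to capture in a trial of safety and feasibility.

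No other planned analysis puts these patients back into the success rate. The per-protocol set is narrower still and removes them too. The set of all who started would include them, but it is used only for safety endpoints.

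The label is also wrong. A set that depends on how long treatment lasted after randomisation is not intention-to-treat.

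**Working it through.** **1. Reproducing the stated design.** The inputs from Statistical methods are success rates of 0.65 (null) and 0.85 (alternative), power 0.80, 21 patients at the interim (taken per arm, since each arm is assessed separately), a maximum of 52, and expected sizes of 25.59 and 29.97. The article does not print the boundaries. A search over exact binomial two-stage designs, minimising the expected size under the alternative, gives this rule at one-sided alpha 0.025:

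| Successes among the first 21 | Action |
|---|---|
| 15 or fewer | stop for futility |
| 16 | 31 more, need 26 successes among them |
| 17 | 17 more, need 14 |
| 18 | 9 more, need 7 |
| 19 or more | stop for success |

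- Expected size at 0.65: 21 + 0.1085×31 + 0.0593×17 + 0.0245×9 = 25.59.
- Expected size at 0.85: 21 + 0.1147×31 + 0.1912×17 + 0.2408×9 = 29.97.
- Maximum: 21 + 31 = 52.
- Attained alpha at 0.65: P(19 or more) + Σ P(x)·P(stage 2 succeeds) = 0.0086 + 0.1085×0.0177 + 0.0593×0.1028 + 0.0245×0.3373 = 0.0249.
- Power at 0.85: 0.800.

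All the stated sizes are matched. At the stated one-sided 0.05, the same search gives 23.10 and 24.25 with a maximum of 36, which does not match. That discrepancy is a separate point. Here it means only that the baseline of 0.025 comes from a reconstruction, while the level the protocol states is 0.05.

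**2. Effect of leaving out early failures.** Let d be the share of all who start and then stop in week 1 for a treatment-related reason. The documents give no value, so d is an assumption. Every patient dropped is a failure. If true success among starters is 0.65, the analysed rate is therefore

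q = 0.65 / (1 − d),

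and the chance of a false success is the rejection probability of the rule above at q.

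| d (assumed) | analysed rate q | P(false success) per arm |
|---|---|---|
| 0 | 0.650 | 0.025 |
| 1% | 0.657 | 0.030 |
| 2% | 0.663 | 0.035 |
| 3% | 0.670 | 0.042 |
| 5% | 0.684 | 0.060 |
| 10% | 0.722 | 0.142 |

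The probability reaches the stated 0.05 at d of about 4% (0.0504 at d = 4%). If all starters are analysed and these patients count as failures, it stays at 0.025 for every d.

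**3. Effect on the estimate.** An analysed success rate of 85% corresponds to 0.85×(1 − d) among all starters: 83.3% at d = 2%, 80.8% at 5% and 76.5% at 10%.

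**4. Effect of a single patient at the interim.** With 19/21 = 90.5% the arm stops for success. One early failure left out makes the rate among starters 19/22 = 86.4%; two make it 19/23 = 82.6%. If one such patient stood among the 21 in place of a success, the count would be 18/21 and the arm would continue with 9 more patients.

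**The case against.** The strongest objection is that the problem may hardly arise. Treatment is outpatient and lasts two to three weeks, and only treatment-related stops in the first 5–6 fractions matter. The 35% null rate equals the wound complication rate that the Background quotes for preoperative radiotherapy, which suggests that discontinuation was given little separate weight in planning. At the expected sizes, d = 2% is about half a patient per arm (0.02×25.59 = 0.5; 0.02×29.97 = 0.6), and d = 10% is about three. This stands: the size is unknown and may be small. It does not remove the conflict between the two definitions.

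A second objection is that all analyses are called descriptive, and that early stoppers remain visible in the safety evaluation, the weekly recording of acute events and the monitoring board's review. This limits the consequence for safety oversight. It does not return the patients to the success rate, and the same section relies on specified error rates and stop-or-continue boundaries.

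A reader might infer more than the documents support:

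- *That the test exceeds its stated error rate.* Under the reproduced rule this happens only above d of about 4%, and no passage shows that d is that large.
- *That separate denominators for efficacy and safety are themselves a fault.* They are ordinary. The fault is the mismatch with an endpoint that counts discontinuation.
- *That the between-arm secondary comparisons should use all randomised patients.* Under Secondary endpoints, local progression-free, disease-free and overall survival are timed from the start of radiotherapy. A patient who was never irradiated has no time origin, so that change would need new endpoint definitions.

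**Conclusion.** The point holds as a conflict between definitions. Followed as written, the plan leaves some endpoint failures out of the primary rate, and the resulting bias can only favour success. This conclusion needs no assumption about d.

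The size does. It depends on d, for which the documents offer no source, and on the reconstructed boundaries. The false-success probability per arm rises from 0.025 to between 0.030 and 0.142 for d from 1% to 10%; the upper end is an extreme scenario, not an expectation. What makes the point worth acting on is the small sample: at the 21-patient interim, one patient separates stopping for success from continuing. It should be fixed, but it does not invalidate the design.

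**What to change.** Base the primary endpoint analysis, including the count of 21 at the interim, on all eligible randomised patients who received at least one fraction. This is the started-treatment set that the plan already uses for safety, limited to eligible patients. State that a treatment-related stop in week 1 is a failure. Keep the set with the one-week minimum only as a sensitivity analysis, and do not call it intention-to-treat. The time origins of the secondary endpoints need no change.

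For the primary endpoint this is a change of definition in the text. Its downside is that the estimated success rate may be slightly less favourable.
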